### Inflammatory markers

Stress is related to low-grade inflammation, as measured by C-reactive protein (CRP) and proinflammatory cytokines such as interleukin-6 (IL-6), tumor necrosis factor (TNF-α), interleukin-1 beta (IL-1β), and interferon-gamma (IFN-γ) [83–88] as well as increased CMD risk [89]. We will assess the relationship between inflammatory burden IL 6, TNF, IL-1B, IFNG, and CRP and change in methylation among the study samples. See the ‘Genomic Data Analysis’ section below for a description of the analysis with the inclusion of individual inflammatory protein measures.

## Methods

This research was approved by Loyola University’s Institutional Review Board (IRB) Protocol number LU214133 WCG IRB #20230283. This study is registered through ClinicalTrials.gov, registration number: NCT05902741. It is estimated that the recruitment of participants will begin summer of 2023.

### Procedures

Detailed descriptions of this study have been previously discussed [90]. Briefly, this convenience sample will include 300 self-identified AA women residing in either the Chicagoland (n = 150) or New York City (n = 150) area between the ages of 50 and 75 years with risk factors for CMD [91]. Participants will be randomized to either an 8-week RiSE intervention or a Health Education Program (HEP) (attention control). Potential participants will be pre-screened for eligibility over the phone and will be followed by an appointment for further screening if the potential participant is eligible. After collecting informed consent for obtaining inflammatory markers and DNAm samples, the samples will be stored in a lab for processing and frozen for later batch analysis. DNAm samples will be stored at 4°C. Specimens will be shipped overnight on dry ice to respective labs for analysis per best practice guidelines [92]. Individuals will contribute data for up to four-time points (baseline, 4 weeks (mid-intervention), 8 weeks (completion of intervention), and 6 months post-intervention). Data will be collected from participants using an Audio Computer-Assisted Self-Interview system (ACASI) [93]. Perceived stress, depression, fatigue, and sleep disturbance symptoms will be analyzed via the Perceived Stress Scale (PSS-10) [94], Patient Health Questionnaire 9 (PHQ 9) [95], NIH PROMIS Fatigue Short Form 8a [96], and NIH PROMIS Short Form v1.0 [97].

### DNA sample collection

Salivary DNAm will be measured at baseline and 6 months following the intervention. Saliva was selected as the sample of choice as it correlates well with DNAm in blood [98–100], is more similar to patterns of DNAm in the brain as compared to blood [101–102], associates with CMD indices [103], and correlates with frontolimbic brain function [104, 105] and therefore, potentially offering distinct opportunities for studies considering psychological measures function [104, 105].

Participants will collect saliva samples using the Oragene-DNA (OG-510) kit that requires them to spit saliva into a tube up to the 1mL mark. Taylor et al. have described details of DNA collection and analysis procedures elsewhere [106]. Samples will be refrigerated at 4 C° in a lab until DNA extraction and analysis are completed. All analysis of DNA extraction will be done at Columbia University under the guidance of [name]. Samples collected at Loyola University will be shipped at ambient temperature to Columbia University for processing and analysis. All tubes and plates that contain an individual’s DNA will be labeled with a barcode to ensure precise sample tracking and recorded in the laboratory’s computerized freezer inventory via barcodes upon arrival at the laboratory.

### Genotyping

The Illumina Infinium Global Diversity Array (GDA) will be used to assess the targeted candidate genes (**Table 2**) and for ancestry informative markers (AIMS). AIMS are included on the GDA chips for multiethnic populations which is suited for our sample of AA women. The GDA combines highly optimized multiethnic, genome-wide content with curated clinical research variants. We selected the GDA chip because it has expanded coverage of SNPs for multiethnic populations [106].

### DNAm analysis

The Illumina Infinium Methylation EPIC v2.0 (900K) BeadChip will be used for examining the methylation of targeted candidate genes [107]. We will apply standard quality control measures including accounting for cell type, batch, and plate effects. This BeadChip directly quantifies DNAm at 936,866 CpG dinucleotides, giving near complete coverage of known genes [107–109]. We will perform hybridization on a per-sample basis. The Infinium arrays are well annotated for CpG dinucleotides in CpG island and non-CpG island promoters, shore regions, coding regions, repetitive elements, miRNA promoter regions, FANTOM5 enhancers, ENCODE open chromatin and enhancers, and DNase hypersensitivity sites and include 91.1% of the loci from the HumanMethylation450 BeadChip. DNAm is determined at each of the CpG sites on the 935K array by measuring the fluorescent signals from the M (methylated) and U (unmethylated) probes specific for each site included in the array, covering approximately 99% of all RefSeq genes and 96% of CpG islands [110]. We will confirm DNAm by methylation-specific polymerase chain reaction (PCR) and by bisulfite sequencing [111]. We may explore the use of additional methylation data in the future to identify additional novel individual genes with abnormal gain and/or loss of CpG methylation associated with social and CMD features for future studies. Additional data from the BeadChip will be retained for future analyses as new information regarding epigenomic differences associated with CMD risk and social factors are described in the literature.

### Data analytic plan

#### Power analysis

We will focus primarily on the tested CpG sites that are true positives, i.e., detected CpG sites with meaningful differential DNAm. There is currently no standard threshold for meaningful differential DNAm, though previous studies have used thresholds of 5–20% [112] for meaningful differential DNAm, and for this study, we use a conservative threshold of 10%. Using the R package ‘pwrEWAS’ [113], we performed simulations to evaluate sample sizes required to detect effect sizes (percent differences) of 7.5%, 10%, 12.5%, and 15% in CpG-specific methylation across 4000 CpGs on our 20 candidate genes with at least 80% power. We need 200 total subjects (150 per group) to detect a difference of at least 10% with at least 80% power across a set of CpG sites (**Fig 3**). Our simulations also indicated that the power to detect at least one differentially methylated CpG out of the set of 4000 is above 85%.

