OXTR	Encodes oxytocin receptor and is associated with range of psychological responses [64]	COMT	Instructs enzyme that regulates neurotransmitters associated with stress [65]
IL-6	Regulates proinflammatory cytokine IL-6 [66]	OPRM1	Provides instructions for making mu opioid receptor which is associated with PTSD [67]
NR3C1	Encodes glucocorticoid receptor associated with stress response and CMD [68–70]	KITLG	Inhibitory role on natural killer cells. Associated with cortisol stress reactivity [71]
AVP	Encodes member of vasopressin/oxytocin family. Plays role in glucocorticoid signaling [62]	DNMT-1	Provides instructions for making DNA methyltransferase 1 which is associated with stress response as well as CMD [4, 72, 73]
GABA	Provide instructions for making GABAA receptor protein which produces calming effect [74]	HSD11β2	Implicated in glucocorticoid regulation and response to stress. Associated with CVD [75, 76]
MAOA	Regulates monoamine oxidase A that is related to psychosocial stress [77]	ACE	Regulates angiotensin converting enzyme which is associated with depression and CVD [78]

Our candidate genes were selected based on those consistently associated with stress response in the literature (see **Table 2**). Several studies have demonstrated that DNAm can be modified within weeks to months following changes in environmental factors [79–81]. In those previous studies of longitudinal change of DNAm, a large variation of inter-individual differences over time has been observed [82]. Therefore, our proposed 6-month follow-up not only provides a reasonable time frame to investigate the longitudinal change in DNAm but also links to socio-behavioral stressors among AA women, which have not been previously studied.

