#### Genomic data analysis

Using the pre-processed and quality-controlled methylation data expressed as beta values which are the percentage methylation at each CpG site at specific targeted candidate genes, we will determine changes in methylation (Δ***β***) at every site as the difference between methylation at baseline and methylation at post-intervention. Negative Δ***β*** indicates a decrease in methylation from baseline to post-intervention, and a positive value indicates an increase in methylation from baseline to post-intervention. Association analyses will be performed to detect differentially methylated sites on the targeted candidate genes between the intervention and non-intervention groups using the Δ***β*** with adjustment for age, health behaviors, early life adversity, hybridization batch, and top principal components of the probes as covariates. To adjust for multiple testing, we will use False Discovery Rate (FDR) adjustment with an FDR of <0.05 regarded as statistically significant. All analyses will be performed in R software using the Bioconductor R package ‘limma’ [115]. To assess the relationship between inflammatory burden (IL-6, TNF-α, IL-1β, IFN-γ, CRP) and Δ***β*** among the study samples, we will repeat the above association analyses with the inclusion of individual inflammatory protein measure.

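### The stated DNAm power is not shown to apply to the planned between-arm test of Δβ, which omits baseline β; adjusting for baseline β would make a single-visit figure a floor

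*Protocol article*

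**What the plan says.** **Power analysis section.** The article reports that "we performed simulations to evaluate sample sizes required to detect effect sizes (percent differences) of 7.5%, 10%, 12.5%, and 15% in CpG-specific methylation". The simulated set is 4000 CpGs in the 20 candidate genes, and the aim was power of 80% or more. The result is given as "We need 200 total subjects (150 per group) to detect a difference of at least 10% with at least 80% power across a set of" tested sites. The chance of finding at least one differential site is also given: "the power to detect at least one differentially methylated CpG out of the set of 4000 is above 85"%. The section mentions no change score, SD of change or correlation between visits. On the target effect it notes that "previous studies have used thresholds of 5–20% [112] for meaningful differential DNAm", and adds that "for this study, we use a conservative threshold of 10"%.

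**Genomic data analysis section.** The analysed quantity is Δβ, defined at each site "as the difference between methylation at baseline and methylation at post-intervention". It is compared between arms in limma at an FDR below 0.05. The covariates are age, health behaviors, early life adversity, hybridization batch and top principal components of the probes. Baseline β is not among them.

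**Related statements.** The Introduction, after Table 2, says of earlier longitudinal studies that "a large variation of inter-individual differences over time has been observed". The paragraph after Fig 3 says that ANCOVA will also be used, because it handles chance baseline imbalance and regression to the mean and is generally more powerful. It does not say whether this covers the methylation outcome. The same paragraph says that each planned analysis was powered.

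**The concern.** Under randomisation, the expected between-arm difference in Δβ equals the expected between-arm difference at follow-up, so the size of the effect is not at issue. The variance is. A change score carries the noise of two visits and gains only what the within-person correlation removes. A power figure built on single-visit variability therefore carries over to the Δβ test only near ρ = 0.5, and nothing in the power section shows that the variance of change was used.

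At stake is whether the 80% that justifies the DNAm sample size belongs to the test that will be run. At CpGs whose methylation is weakly correlated over the interval, it may not. A lesser matter is the word conservative. In a sample-size calculation the cautious choice is the smaller effect, and the chosen 10% is twice the smallest threshold the section cites.

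**Working it through.** **The plan's own figure.** It cannot be reproduced from the article. The CpG-level SD, the number of truly differential sites and the error rate used in the simulation are not given, and Fig 3 is not available here. The sentence also does not fix one n: 200 total is 100 per arm, whereas 150 per group is 300 total. The check is therefore calibrated: assume exactly 80% power for a single-visit difference of 10% and ask what follows for Δβ at the same n.

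**Inputs.** From the article: 4000 CpGs, FDR 5%, a 10% target, 80% power. Assumed: ρ; k truly differential CpGs, from 10 to 400; equal variances at the two visits; one common SD.

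**Formulas.**
- Per-test level: α* = 0.05 × 0.8k / (0.95 × 4000). For k = 10, 100 and 400 this is 0.000105, 0.00105 and 0.00421, with two-sided critical values z = 3.878, 3.276 and 2.862.
- Variance relative to one visit: V = 2(1−ρ) for Δβ without baseline β; V = 1−ρ² with baseline β.
- Power = Φ[(z + 0.8416)/√V − z].

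**Example (k = 100, ρ = 0.3, Δβ).** V = 1.4 and √V = 1.183. Then 4.118/1.183 − 3.276 = 0.204, and Φ(0.204) = 0.58.

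**Power at the same n, over k = 10 to 400:**

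| ρ (assumed) | V, Δβ as planned | Power | V, baseline β added | Power |
|---|---|---|---|---|
| 0.2 | 1.60 | 44–53% | 0.96 | 82–83% |
| 0.3 | 1.40 | 54–61% | 0.91 | 85–86% |
| 0.5 | 1.00 | 80% | 0.75 | 92–94% |
| 0.7 | 0.60 | 97–99% | 0.51 | 99% or more |

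Adjustment is never worse than the change score, because 2(1−ρ) − (1−ρ²) = (1−ρ)², which is at least 0. Nor is it worse than a single visit, because 1−ρ² is at most 1.

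**Dependence on n.** Table 1 assumes 125 complete cases per group, and the Discussion plans 250 completers. Multiplying (z + 0.8416)/√V by √(125/n₀), where n₀ is the per-arm size that gives 80%:
- n₀ = 100: power for Δβ at ρ = 0.3 is 72–74%. Break-even is where 2(1−ρ) = 1.25, that is ρ = 0.375.
- n₀ = 150: power for Δβ at ρ = 0.3 is 41–50%. Break-even is where 2(1−ρ) = 0.833, that is ρ = 0.583.

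**The 10% target.** 10/5 = 2, so at a fixed SD a 5% effect needs 2² = 4 times the sample. With the same calibration and V = 1, power is 37–47% at 7.5% and 6–16% at 5%. With V = 0.6 (Δβ at ρ = 0.7) these become about 76–77% and 20–32%. The smallest effect the authors simulated was 7.5%.

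**The case against.** The strongest reply is that the mismatch is inferred. The power section never says single-visit, and Δβ is measured in the same percentage units, so the authors may have simulated a difference in change. A condensed article may also leave the SD or correlation to the full protocol. This stands: a missing ρ is not in itself a fault, and one sentence could settle the question. What remains is that the text ties its 80% to a difference in methylation and its test to a difference in change, with nothing to connect them.

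A reader might infer that the trial is underpowered for DNAm. The documents do not support that. Above ρ = 0.5 the stated power would be too low. The Introduction's remark about large inter-individual variation gives no ratio of change variance to single-visit variance, so it cannot place ρ below 0.5.

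It can also be said that ANCOVA is already promised. If it covers the methylation outcome, the variance problem largely goes away. But the covariate list for the Δβ model omits baseline β, so the two sections need to be brought together.

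On the threshold, a plan may power on a bar it declares. The field has no standard, 10% lies below the 12.5% midpoint of the cited range, and 7.5% was simulated too. A reader might also infer that the authors would take a null result to exclude 5% effects; the article makes no such claim. Only the label is at fault.

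**Conclusion.** The point holds in a limited form. The stated 80% or more is not shown to apply to the planned Δβ comparison. If the simulation was single-visit, the figure is too high at CpGs with ρ below 0.5 and too low above it, and the direction for this trial is unknown. The illustrative sizes rest on an assumed ρ, an assumed number of true sites, a common SD, and 80% holding exactly at 10% and at an unchanged n. They cannot be firmed up until the contradictory sample-size sentence is resolved. It would go too far to say that the 80% is wrong for the planned test, since the text leaves open that Δβ was simulated. The case for adding baseline β does not depend on how that question is answered. The 10% label is a secondary wording point.

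**What to change.** 1. In the Genomic data analysis section, add each CpG's baseline β as a covariate, in line with the article's own ANCOVA rationale. The data are already collected at baseline. The cost is programming: the covariate differs by site, so the model fit must allow a site-specific design.
2. In the Power analysis section, say whether the simulated difference was in Δβ.
3. Reconcile the 200 total with the 150 per group, then restate power for the baseline-adjusted contrast at 125 completers per arm. A single-visit simulation at that n can be reported as a floor. If Δβ without baseline adjustment is kept, show power over a range of ρ. The cost is a simulation re-run, and the stated figure may become less favourable.
4. Drop the word conservative for the 10% target, or report power at 5% alongside it. This is a wording change or one more simulated effect size.

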**Fig 1 pone.0295293.g001:**
[figure not shown]
Study period. Schedule of enrollment, interventions, and assessments.

**Table 1 pone.0295293.t001:** Sample size estimation based on preliminary date. *Assumes n = 125 per group complete cases and *α* = 0.05; r-squared of 5 covariates is 0.30, **The smallest mean difference necessary to ensure > 80% power, assuming pooled SD observed in the pilot.

Outcome evaluated at 6 months	RiSE Mean	Control Mean	|Δ| Means	Pooled SD	Effect size	Power*	Mean difference for 80% power**
	Observed: Pilot Data @ 8 weeks						
WCQ-Active coping	23.76	24.77	1.01	8.24	0.06	21%	2.45
WCQ-Avoidance coping	8.14	14.38	6.24	5.25	0.59	>99%	1.56
WCQ-minimize situation	11.21	14.04	2.83	4.36	0.32	>99%	1.30
DASS-21: Depression	1.45	3.13	1.68	3.09	0.27	>99%	0.92
DASS-21: Anxiety	2.39	3.31	0.92	3.41	0.13	72%	1.02
DASS-21: Stress	4.45	5.90	1.45	4.05	0.18	92%	1.20
TNF-a	0.95	1.00	0.05	0.36	0.07	26%	0.11
High-sensitivity C-reactive protein (hsCRP)	3.83	7.24	3.41	6.30	0.27	>99%	1.88

*Resilience*, *Stress*, *and Ethnicity* (RiSE) [37–39], is a group-based, 8-week intervention that integrates cognitive-behavioral strategies [40] focused on the biopsychosocial impact of racism [41, 42], racial identity development [43–45], and empowerment [46]. The conceptual model for the study is based on allostatic load theory [47] which posits that accumulating stress or “wear and tear” results in negative physiological consequences. **See Fig 2.**

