## Discussion

### Potential pitfalls, alternative approaches

Given the longitudinal nature of this study and the significant commitment necessary to participate in the study, attrition is an inherent potential issue. In our preliminary work, we found an 11% attrition rate with a similar design. For this study, we will conservatively over-sample by 20% to accommodate potential attrition to achieve n = 250 participants with complete data at 6 months. We will minimize attrition by collecting multiple phone and email/text messaging contact information for participants and reviewing this information at each visit. It is possible that some participants may not have access to the internet or have technical challenges with Zoom. We will provide iPads and internet access for participants who lack equipment and/or internet access. In addition, our study team will teach participants how to use Zoom as needed and be available in real time to address technical issues. To note, synchronous online platforms have successfully been used to administer group-based psychobehavioral interventions, including in older populations [116–119]. Further, we have experience successfully conducting research groups via Zoom ([name]: PCORI). Despite these limitations, the proposed study will be designed and implemented with the highest degree of scientific rigor and has the potential for significant public health impact. Finally, by providing concrete recommendations based on the results of this intervention, we believe that this is the first study to provide the needed science to implement interventions focused on reducing the impact of multiple forms of stressors on the CMD health of AA women by exploring the biological changes in DNAm and inflammation that may contribute to this disparity.

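### The methylation sample size is given as 200 in total and as 150 per group; neither matches the 125 per group expected with complete data, so the 80% power claim is tied to no one design.

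*Protocol article*

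**What the plan says.** The Power analysis section of the protocol article reports a pwrEWAS simulation for differences "in CpG-specific methylation across 4000 CpGs on our 20 candidate genes with at least 80% power". It takes 10% as the meaningful difference and concludes: "We need 200 total subjects (150 per group) to detect a difference of at least 10% with at least 80% power". It does not say whether these numbers count women enrolled or women analysed.

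The other sample-size statements in the article are:

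- Procedures: "this convenience sample will include 300 self-identified AA women", half at each of two sites, randomized to RiSE or to an attention control.
- Potential pitfalls, alternative approaches: a 20% over-sample "to achieve n = 250 participants with complete data at 6 months".
- Table 1 caption (coping, DASS-21 and inflammatory outcomes): "Assumes n = 125 per group complete cases".

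Saliva for methylation is taken at baseline and 6 months (DNA sample collection). The outcome is the change at each CpG between the two samples (Genomic data analysis), and for the tests "we will use False Discovery Rate (FDR) adjustment with an FDR of <0.05 regarded as statistically significant".

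**The concern.** In a two-arm trial a total of 200 and a group size of 150 cannot both be right. Unequal allocation does not reconcile them, because a per-group figure fixes both arms. Nor does dropout inflation, because the total is smaller than the sum of its groups.

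The number that determines power is the number of women with both saliva samples. By the article's own attrition allowance that is about 125 per group, which lies between the two readings (100 and 150). If 150 per group is the requirement for analysis, the plan falls 25 per group short of it. If 200 in total is the requirement, the plan exceeds it and the figure in brackets is wrong.

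Methylation change is the subject of this article and this sentence is its only sample-size basis. The same section goes on to say that every planned analysis was adequately powered, which the sentence cannot support as printed. A null methylation result could be read against the wrong power.

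**Working it through.** **1. Totals and group sizes.** Two arms (Procedures), so total = 2 × n per group.

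- 2 × 150 = 300, not 200.
- 200 / 2 = 100, not 150.

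**2. Number expected for analysis.** Enrolled 300 (Procedures); 250 with complete data at 6 months (Potential pitfalls).

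- 300 / 1.20 = 250, or 125 per group.
- Taken as a 20% loss from 300: 300 × 0.80 = 240, or 120 per group.
- At the 11% attrition of the preliminary work: 300 × 0.89 = 267, or about 133 per group.

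None of these leaves 150 pairs per group.

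**3. Is 125 per group the article's working number?** Table 1 can be recomputed. Take SD × √(1 − 0.30) for the covariate R² of 0.30, two-sided α = 0.05, and power = Φ(Δ / (SD_adj × √(2/n)) − 1.96). Example, DASS-21 anxiety at n = 125: SD_adj = 3.41 × √0.70 = 2.853; standard error = 2.853 × √(2/125) = 0.361; 0.92 / 0.361 = 2.549; Φ(2.549 − 1.96) = 72.2%. For the four rows printed below 99%:

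| Outcome | Printed | n = 100 | n = 125 | n = 150 |
|---|---|---|---|---|
| Active coping | 21% | 17.8% | 21.1% | 24.5% |
| DASS-21 anxiety | 72% | 62.6% | 72.2% | 79.7% |
| DASS-21 stress | 92% | 85.7% | 92.3% | 96.0% |
| TNF-α | 26% | 21.6% | 25.9% | 30.1% |

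Only 125 per group reproduces the table. Table 1 has no methylation row. Using 125 for methylation is an inference from the trial-wide target of 250 completers and from an outcome that needs the 6-month sample.

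**4. What the two readings imply at 125 per group.** The simulation itself cannot be repeated: the text gives no SD, tissue or number of truly differential CpGs, and Fig 3 is not available here. Power can still be rescaled from one n to another under stated assumptions:

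- power is exactly 80% at the reference n, for a 10% difference;
- 4000 CpGs, of which k truly differ (k = 10 to 400, an assumed range);
- FDR 5%, which implies a per-CpG threshold α* = (0.05/0.95) × 0.80k / (4000 − k), two-sided with critical value z*.

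Power at the new n = Φ((z* + 0.8416) × √(n_new/n_ref) − z*).

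| k | α* | z* | 150 → 125 per group | 100 → 125 per group |
|---|---|---|---|---|
| 10 | 0.00011 | 3.878 | 66.7% | 91.9% |
| 40 | 0.00043 | 3.524 | 67.8% | 91.3% |
| 100 | 0.0011 | 3.269 | 68.6% | 90.8% |
| 400 | 0.0047 | 2.828 | 69.9% | 89.9% |

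If 150 per group is the reference, the difference detectable with 80% power at 125 per group is 10% × √(150/125) = 10.95%. At the pilot's attrition (about 133 per group) power would be about 71–74%.

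**5. Sensitivity to the threshold.** With fixed per-test levels of 0.05, 0.001 and 0.05/4000 in place of the FDR-implied ones, 125 per group gives 73%, 69% and 65% if 150 is the reference, and 88%, 91% and 93% if 100 is the reference. The direction does not change.

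**The case against.** The strongest reply is that this is a transcription slip in a sound simulation. Half of the 300 enrolled is exactly 150, so 150 per group may be the enrolment figure and 200 a misprint for 300. The gap between 150 and 125 would then be the planned attrition allowance. Equally, if 200 in total is right, 250 completers exceed the requirement. A required number need not equal the expected number of completers; it only must not exceed it. Fig 3 plots the simulated power and may show which n was meant.

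The 67–70% figure also needs power of exactly 80% at 150 per group, whereas the text says at least 80%. If power at 150 were 90%, the same formula gives about 80–82% at 125, which is no real shortfall. Finally, the correction alters neither the analysis model nor the data collected.

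Much of this stands. Underpowering is not demonstrated, and the power figures are illustrations conditional on their assumptions. What does not fall away is the contradiction: the printed sentence is impossible, nothing else in the text says which half is right, and a figure cannot make the sentence consistent. On the enrolment reading the claim is still wrong in substance, because power would be quoted at the number enrolled for an outcome that only women with both samples can contribute to.

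**Conclusion.** The concern holds. The stated methylation sample size is arithmetically impossible for a two-arm trial, and neither half of it is the 125 per group that the article plans to have with complete data. The printed text does not settle whether the trial is above or below its stated 80% power.

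At 125 per group, power for a 10% difference is about 67–70% if 150 per group was the requirement and about 90–92% if 200 in total was. These figures assume exactly 80% at the reference n, a 5% FDR over 4000 CpGs, and 10 to 400 truly differential sites; other thresholds widen the ranges to 65–73% and 88–93%. Because this is the sole sample-size basis for the article's main aim, it must be corrected.

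**What to change.** Read the existing pwrEWAS output, or re-run it, at the number expected to be analysed: 125 per group, 250 in total, with both saliva samples. Replace the sentence with one total and one per-group number that agree, say that they count women with paired samples, and give either the power for a 10% difference or the smallest difference detectable with 80% power at that number. Check the statement about detecting at least one differential CpG at the same n.

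The cost is one simulation run and a corrected sentence. The correction does not itself call for a change to enrolment, conduct or the analysis model. The restated power may be less favourable than the present claim, and if so it should be reported as it is.
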